### Sample size

ES for CBM-I to alter IB are moderate to large in youth (*g* = 0.52–0.70) [112]. The ES of CBM-I on cortisol stress response in high-risk youth is difficult to estimate due to inconsistent findings and the lack of research on this specific topic in general. One meta-analysis of studies with youth found a small effect of CBM-I on self-reported anxiety following a stressor (*g* = 0.34) [112]. However, this effect is likely an underestimate as the studies often involved just 1 or 2 training sessions and samples were largely healthy. Furthermore, CBM-I research in an adult sample found that while positive interpretation training did improve recovery from stress as indexed by physiological changes (heart rate, *f* = 0.58), self-reported stress reactivity remained unchanged between conditions [66].

Calculations using GPower ® software [113] yield a minimum sample size of *N* = 70 participants for the comparison of participants’ stress response from pre- to post-intervention between the two intervention groups, using *g* = 0.34 [112], an α = 0.05 and a ß = 0.80 for two conditions and two measurement time points. A dropout rate of 20% should be accounted for in intervention studies. Overall, this results in a total sample of 88 HR participants at T1. Considering the novelty of the research question and the mixed literature, we decided to be particularly cautious and aim for a sample size of 100 HR participants (*n* = 50 per condition).

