There is also the possibility that the intervention modifies IB but has no effect on participants’ physiological stress reactivity. This would indicate that IB does not have a strong casual role in an altered stress responses. On a clinical level, this would indicate that IB interventions may be limited in their efficacy and that alternative approaches, such as a more explicit training during a stressful event may be more beneficial. Regardless of the findings, the proposed RCT will have important theoretical implications for existing models of the familial transmission of depression, which act as a theoretical foundation for many intervention studies.

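### The stated sample sizes (70, 88, 100) do not give 80% power for a between-arm effect of g = 0.34; the setting that reproduces 70 corresponds to 0.68 SD

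*Protocol article*

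**What the plan says.** The Sample size section of the protocol article takes its effect size from a meta-analysis in youth that "found a small effect of CBM-I on self-reported anxiety following a stressor". It applies this to the comparison of the "pre- to post-intervention between the two intervention groups, using *g* = 0.34", with an "α = 0.05 and a ß = 0.80 for two conditions and two measurement time points". The result is a minimum of 70. After 20% dropout, "Overall, this results in a total sample of 88 HR participants at T1", and the target is then set at 100 (50 per arm) as a precaution. The section does not name the G*Power test, the conversion of g to the f that G*Power uses, or the T1–T2 correlation.

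The Hypothesis testing section tests H5 and H6 by an ANOVA with condition as the factor, and says that confounders, including baseline cortisol response, will be accounted for. The Discussion considers the case in which the intervention changes interpretation bias but not the stress response, and concludes: "This would indicate that IB does not have a strong casual role in an altered stress responses".

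**The concern.** A standardised mean difference of 0.34 between two parallel arms is a small effect, and 70 children in total is few for it. A two-sample comparison at d = 0.34 needs about 274 for 80% power. A repeated baseline can reduce that number, but a reduction to 70 requires a very high T1–T2 correlation.

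Stress reactivity and recovery are primary outcomes and carry the trial's central question. If power for the effect the protocol names is well below 80%, the stated justification misinforms readers. A non-significant cortisol result would also be weak support for the conclusion that the Discussion has ready for it.

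**Working it through.** **Inputs.** From Sample size: g = 0.34, α = 0.05, power 0.80 (printed as ß), two groups, two time points, N = 70, 20% dropout, 88, 100. From Hypothesis testing: adjustment that includes baseline cortisol response. Assumptions: two-sided test, equal arms, and T1–T2 correlation ρ, which is not given and is taken as 0.5 with 0.3 to 0.8 shown.

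**Step 1. Reproduce the plan's figure.** For the repeated-measures within-between interaction with m = 2 times, λ = f²·N·m/(1 − ρ), df = 1 and N − 2. With f = 0.34/2 = 0.17 and ρ = 0.5:
- N = 70: λ = 0.0289 × 70 × 2/0.5 = 8.09, power 0.801
- N = 68: λ = 7.86, power 0.789

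So N = 70 is returned, and 70/0.8 = 87.5 gives 88. With f = 0.17 and ρ = 0, 0.3, 0.6 or 0.7, the same test returns 138, 98, 58 or 44.

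Two other routes also return 70: 0.34 entered directly as f in a one-way two-group ANOVA, and 0.34 entered as dz in a paired t-test. Neither is a calculation for two conditions and two time points.

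**Step 2. What these entries mean.** Suppose the arms are equal at T1, as randomisation gives in expectation, and differ by d SD at T2. Each of the four cells then departs from additivity by d/4, so the interaction f is d/4.
- f = 0.17 corresponds to d = 4 × 0.17 = 0.68.
- d = 0.34 corresponds to f = 0.34/4 = 0.085.

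The relation f = d/2 belongs to a one-factor comparison of two groups. In that setting f = 0.34 again means d = 0.68. The paired t-test compares no arms at all. None of the three routes gives 80% power for a between-arm 0.34.

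**Step 3. Power for a true 0.34.** With f = 0.085 and ρ = 0.5, λ = 0.007225 × N × 2/0.5:
- N = 70: λ = 2.02, power 29%
- N = 80 (100 less 20%): λ = 2.31, power 32%
- N = 88: λ = 2.54, power 35%
- N = 100: λ = 2.89, power 39%
- N = 274: λ = 7.92, power 80%

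For other correlations the noncentral t is used. The noncentrality is 0.34·√(N/4)/√(2(1 − ρ)) for group-by-time (df N − 2) and 0.34·√(N/4)/√(1 − ρ²) for ANCOVA on baseline (df N − 3).

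| ρ | Group-by-time, N = 80 | ANCOVA, N = 80 | Group-by-time, N = 100 | ANCOVA, N = 100 |
|---|---|---|---|---|
| 0.3 | 25% | 35% | 30% | 42% |
| 0.5 | 32% | 41% | 39% | 49% |
| 0.7 | 49% | 56% | 58% | 65% |
| 0.8 | 66% | 71% | 76% | 80% |

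ANCOVA at ρ = 0.5 needs N = 206 for 80% power. For 70 to suffice with the group-by-time test, ρ would have to be about 0.87. At 0.875 the f = 0.17 route would have returned 20, not 70.

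**Step 4. Detectable effect and precision at N = 80.** The difference detectable with 80% power is 0.60, 0.55 and 0.45 SD for ANCOVA at ρ = 0.3, 0.5 and 0.7, and 0.63 SD for group-by-time at ρ = 0.5. The 95% confidence interval half-width is t × SD × √(4/N). At ρ = 0.5 it is 0.39 SD (ANCOVA) or 0.45 SD (group-by-time). At ρ = 0.7 it is 0.32 SD with ANCOVA.

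**The case against.** Several points on the other side are fair.

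- **The route is not documented.** A reader might infer that the plan demonstrably entered g/2 as an interaction effect. The section does not say so, and two other entries also return 70. The description "a ß = 0.80 for two conditions and two measurement time points" makes the interaction route the most plausible, no more. The shortfall does not depend on which route was used.
- **A single low power figure is not supported.** A reader might infer that true power is 30–40%. That range belongs to the group-by-time test at ρ = 0.5. If the planned adjustment for baseline cortisol response applies to H5 and H6, the analysis is closer to ANCOVA and power is 41–49% for N = 80 to 100 at ρ = 0.5, and more at higher correlations.
- **Consequences for a null result are conditional.** A reader might infer that a non-significant result is the likelier outcome whenever 0.34 is true, or that even an observed zero could not exclude 0.34. With ANCOVA at N = 80 and ρ = 0.7, power is 56% and the half-width is 0.32 SD, so neither statement holds there.
- **The effect may be larger.** The section says that the effect is hard to estimate and that 0.34 is probably too low. That is reasonable context, but 0.34 is the value the calculation is said to use. A larger target would have to be named.
- **The Discussion sentence is not a decision rule.** It is conditional, it speaks only against a strong causal role, and Bayes factors are planned. They are framed as a means of rejecting the null, however, so they soften the point without removing it.

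**Conclusion.** The concern holds in this form: the printed N does not follow from the printed effect size at 80% power. The setting that best explains 70 corresponds to a between-arm difference in change of 0.68 SD, twice the cited 0.34. For a true 0.34 and 80 analysable children, power is roughly 25–49% (group-by-time) or 35–56% (ANCOVA) over correlations of 0.3 to 0.7. Within correlations up to 0.8, 80% is reached only with ANCOVA, all 100 children analysed and a correlation of about 0.8.

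This rests on g being a between-arm difference in SD units of the outcome, on arms equal at T1, and on a two-sided 5% test. If 0.34 is instead standardised by the SD of change, power is 29%, 32% and 39% at N = 70, 80 and 100 whatever the correlation. The exclusion of children who complete less than 80% of the training would lower the analysed N further, unless it is already counted in the 20%.

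This is not an omission that an analysis plan could fill, because the sample size justification itself is wrong as printed.

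**What to change.** Keep N = 100 and correct the justification in the Sample size section:

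1. Name the G*Power test, the conversion of g to f and the assumed T1–T2 correlation, and write 1 − ß = 0.80.
2. Replace the power claim with the detectable effect. For example: with about 80 analysable children the trial has 80% power for a between-arm difference of about 0.55 SD (ANCOVA, correlation 0.5; about 0.60 to 0.45 SD for correlations of 0.3 to 0.7). Without baseline adjustment, the group-by-time figure is about 0.63 SD at correlation 0.5.
3. Give power for 0.34 as a range, for example 35–56% with ANCOVA at N = 80.

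In the Discussion, state that a non-significant cortisol result counts against a causal role only if the confidence interval excludes a pre-stated smallest relevant effect, or if an equivalent pre-stated criterion is met, such as a Bayes factor for the null. Otherwise the result is inconclusive.

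The cost is rewording one section and one Discussion statement, and a less favourable stated power. No additional participants are needed.

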#### Cortisol data preparation

First, we will check the distributional characteristics of the baseline cortisol data (i.e., cortisol levels pre-TSST-C at session 1). It is expected that some participants will have high baseline cortisol concentrations and that these participants will be unable to elicit a cortisol response to the laboratory stressor (suppression of HPA axis response due to negative feedback [110]). Without knowing the distribution of cortisol values, it is difficult to determine a numerical cut-off. Therefore, we plan to exclude participants whose baseline cortisol levels are significantly higher from other cases in the distribution. We will transform the remaining cortisol data into standardized values (z-scores) and check for outliers by inspecting the respective histograms for each cortisol variable. We will consider z-scores above + 3.29 or below -3.29 as outliers. Once outliers are removed, we will determine the normality of all cortisol variables using the Shapiro–Wilk-Test. If more than one cortisol variable fails the test for normality, all cortisol values will be log transformed before further analyses are conducted.

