#### Hypothesis testing

To test the hypotheses that HR children have more negative IB (H1) and altered cortisol reactivity and recovery (H2, H3) when compared with LR children at T1, t-tests will be performed using IB, cortisol reactivity and recovery as dependant variables (DVs) and group membership (HR, LR) as the independent variable (IV). No specific predictions about the direction of effects for participants’ cortisol reactivity (H2) are made given the mixed literature [18]. For cortisol recovery (H3), it is predicted that HR participants’ cortisol levels will take longer to return to baseline after experiencing the laboratory stressor [47, 111]. Furthermore, to account for the possible confounding variables assessed in this study, a regression model will be run for the effect of group on IB, including age, depression and anxiety symptoms, childhood trauma, sex and pubertal status as covariates. The association between baseline IB and stress response will be looked at within each group (HR and LR) as well as in the entire sample using bivariate correlation. Bayes Factors will be calculated to warrant a rejection of the null hypothesis.

To determine whether the IB training was indeed more effective than the placebo training (H4) in HR individuals, a manipulation check will be conducted using ANOVA. In line with a previous study, participants who complete less than 80% of the training will be excluded from analyses [85].

To test the hypothesis, that the active (versus placebo) IB condition exerts effects on HR individuals’ stress reactivity and recovery (H5 and H6), an ANOVA will be conducted with the condition as the IV (active vs. placebo IB intervention) and cortisol reactivity and recovery as the DVs. Exploratory analyses will be conducted to determine the relationship between change in IB and change in stress response in HR individuals. All relevant confounding variables assessed in this study will be accounted for (age, symptoms of depression and anxiety, childhood trauma, sex, pubertal status, baseline cortisol response). Additionally, Bayes Factors will be calculated to determine whether the null hypothesis can be rejected.

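### The step from 70 to 88 children allows for dropout only, so the plan's own exclusions must come out of the margin between 88 and 100, and the article does not say so

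*Protocol article*

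**What the plan says.** The Sample size section takes g = 0.34 from a meta-analysis that "found a small effect of CBM-I on self-reported anxiety following a stressor". With "an α = 0.05 and a ß = 0.80 for two conditions and two measurement time points" (the 0.80 is evidently the power), it obtains a minimum of 70 "participants for the comparison of participants’ stress response from pre- to post-intervention between the two intervention groups". It then applies a 20% dropout rate: "Overall, this results in a total sample of 88 HR participants at T1". The target is finally raised to 100, 50 per condition. The reason given is caution, because the question is new and earlier findings disagree. Exclusions are not mentioned.

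Three exclusion rules stand elsewhere in the article:

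- **Training (Hypothesis testing):** "participants who complete less than 80% of the training will be excluded from analyses".
- **Baseline cortisol (Cortisol data preparation):** "we plan to exclude participants whose baseline cortisol levels are significantly higher from other cases in the distribution". The same paragraph expects such children to occur and says that no numerical cut-off can be set in advance.
- **Outlying cortisol values (Cortisol data preparation):** "We will consider z-scores above + 3.29 or below -3.29 as outliers". Outliers are removed before normality is checked.

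The article states no expected rate for any of the three.

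**The concern.** A dropout allowance is meant to turn the number enrolled into the number analysed. Here it covers only one of several ways in which a child can leave the analysis. The two cortisol rules act on the outcome for which the 70 was calculated. The training rule depends on about 20 app sessions over four weeks, completed mostly at home by children aged 10 to 14. The article itself foresees missed sessions and plans reminder emails.

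If exclusions are not counted, the stated 80% power belongs to a number of children that the analysis may not contain. The rise from 88 to 100 then looks like spare caution, although part of it may be needed to absorb planned exclusions.

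**Working it through.** **Inputs from the article:** minimum 70; dropout 20%; inflated total 88; target 100; g = 0.34; α = 0.05; power 0.80; two groups and two time points. **Assumed, because not stated:** pre-post correlation ρ = 0.5, and the fraction e of completers who are excluded.

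**1. The plan's own figures.** For the group-by-time interaction, f = g/2 = 0.17 and the noncentrality is λ = N·f²·m/(1 − ρ) with m = 2. At N = 70 this is 70 × 0.0289 × 2/0.5 = 8.09, which gives power 0.801. The 70 is therefore reproduced at ρ = 0.5. The inflation is 70/(1 − 0.20) = 87.5, rounded up to 88. Both steps are sound as far as they go.

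**2. Room for exclusions.** Completers = N × (1 − dropout); room = whole completers − 70.

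| Dropout | Completers of 88 | Room | Completers of 100 | Room |
|---|---|---|---|---|
| 10% | 79.2 | 9 | 90 | 20 |
| 15% | 74.8 | 4 | 85 | 15 |
| 20% (stated) | 70.4 | 0 | 80 | 10 |
| 25% | 66.0 | −4 | 75 | 5 |

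At the stated 20%, 88 has no room and 100 has room for 10, which is 10/80 = 12.5% of completers. In terms of total loss from all causes, 88 tolerates (88 − 70)/88 = 20.5% and 100 tolerates (100 − 70)/100 = 30%.

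**3. What exclusions would cost.** Remaining = N × 0.80 × (1 − e), with power from the formula in step 1.

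| e (assumed) | From 88 | Power | From 100 | Power |
|---|---|---|---|---|
| 0% | 70.4 | 0.80 | 80 | 0.85 |
| 5% | 66.9 | 0.78 | 76 | 0.83 |
| 10% | 63.4 | 0.76 | 72 | 0.81 |
| 12.5% | 61.6 | 0.75 | 70 | 0.80 |
| 15% | 59.8 | 0.73 | 68 | 0.79 |
| 20% | 56.3 | 0.71 | 64 | 0.76 |

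The headcounts do not depend on the effect size or the test. The power figures do: at ρ = 0.7 the same formula needs only 44 children, and at ρ = 0.3 it needs 98.

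**The case against.** The strongest reply is that 88 is not the target. The trial plans for 100, and 100 absorbs a total loss of 30%. At 20% dropout, more than 12.5% of completers would have to be excluded before the number fell below 70, and nothing in the article shows that this will happen. Even at 20% exclusion, power is about 0.76 under the assumed correlation. This stands, and it limits the point to how the margin is described.

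The training rule may also overlap with dropout, since children who stop training may be the ones who miss T2. It appears in the paragraph on the H4 manipulation check, and the text does not settle whether it reaches the cortisol tests H5 and H6. Both remarks are fair. They could shrink the exclusions that come on top of dropout, but they do not bring the cortisol rules into the allowance.

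A reader might infer three stronger things that the article does not support:

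- **That 88 is miscalculated, or can never leave 70.** The division is correct, and 88 does leave 70 at 20% dropout if nobody is excluded.
- **That every child with one outlying sample is lost.** The screen works on each cortisol variable. A child with one flagged sample among the post-stress values may still have a computable reactivity index. How often any sample is flagged is therefore not a loss rate.
- **That the remark that earlier "samples were largely healthy" is baseless because this trial also enrols undiagnosed children.** The Background reports negative interpretation bias in high-risk children even after their own symptoms are controlled for, and altered cortisol reactivity in healthy children of depressed parents. That is some basis for expecting a larger effect than in unselected samples. In any case the calculation used 0.34 unadjusted.

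**Conclusion.** The point holds in a limited form. The loss allowance and the exclusion rules in the same article do not fit together. At the stated 20% dropout, 88 supplies the minimum only with no exclusions at all, although the plan expects some children with high baseline cortisol and intends to exclude them. The planned 100 supplies it only if at most 10 of 80 completers are excluded.

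Whether 100 falls short cannot be determined, because no exclusion rates are given. If it did, the loss would be modest: power of about 0.79 at 15% exclusion and 0.76 at 20%, under f = 0.17 and an assumed correlation of 0.5. The 12 children added to 88 should not be read as pure caution, since some of them may be needed to cover planned exclusions.

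**What to change.** 1. In Hypothesis testing, base the main analyses of H4 to H6 on all randomised children with T2 data, and present the exclusion of children below 80% of training as a sensitivity analysis. The largest avoidable draw on the margin then disappears, and the randomised comparison is better preserved.
2. In Sample size, state that 100 randomised children leave 70 analysable only if dropout and all remaining exclusions together do not exceed 30%, and that 88 would suffice only with no exclusions.

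An expected loss for each rule need not be given, because the article explains that the baseline-cortisol cut-off cannot be fixed before the distribution is seen.

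No further children are needed. The cost is a less favourable stated margin, and some dilution of the estimated effect because low-training children stay in the main analysis. The sensitivity analysis would still show the result among those who trained as intended.

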## Discussion

Although the lifetime prevalence for children of depressed parents developing depression themselves is up to three times higher than in the general population, there is great potential in improving the support which is available to this vulnerable group. Understanding the underlying mechanisms and how these interact could help reinforce the movement away from interventions comprising general psychotherapeutic tools and towards more targeted prevention. This protocol describes an RCT designed to examine how two proposed mechanisms distinguishing children of depressed parents from low-risk children interact. This will be done by targeting one of these mechanisms, namely IB, through a four-week IB intervention and then determining whether this has a positive effect on individuals’ psychobiological stress response. The proposed RCT will therefore be the first to experimentally test the association between cognitive and physiological vulnerability factors in HR youth.

One-hundred HR individuals will be randomly allocated to receive either an i) IB intervention or a structurally and temporally similar ii) placebo intervention. We hypothesise that in comparison to the placebo intervention, the IB intervention will be effective in significantly improving participants’ IB, which will in turn influence their psychobiological stress reactivity and recovery.

We expect children to benefit greatly from the IB intervention. Through more positive interpretation in ambiguous situations, positive effects on their social life, self-efficiency and physical stress experience are to be anticipated. If this is indeed the case, this approach could be used not only as an add-on to Cognitive Behavioural Therapy for children with depression but also as a preventive measure before the onset of the disease [114–116].

The ability to interpret ones environment more positively could lead to an improved stress response and ultimately may heighten the threshold to the onset of the disease itself. Furthermore, considering IB interventions can be delivered digitally (e.g. on handheld devices) they represent a potentially useful resource for universal or selected prevention [67, 117].

There is also the possibility that the intervention modifies IB but has no effect on participants’ physiological stress reactivity. This would indicate that IB does not have a strong casual role in an altered stress responses. On a clinical level, this would indicate that IB interventions may be limited in their efficacy and that alternative approaches, such as a more explicit training during a stressful event may be more beneficial. Regardless of the findings, the proposed RCT will have important theoretical implications for existing models of the familial transmission of depression, which act as a theoretical foundation for many intervention studies.

